#### 8.4 Withdrawal of individual subjects

Subjects can leave the study at any time for any reason if they wish to do so without any consequences. The investigator can decide to withdraw a subject from the study for urgent medical reasons. In case a participant prematurely terminates his/her participation, s/he will be asked to give permission that the data that were collected until that time point may be included in the ITT-analyses. If the participant refuses to give permission, his/her data will be destroyed.

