This survey will allow them to provide a physical mailing address, so hard copies of consent and informational materials can be mailed to them. Screening questions will also include items about age, Dutch fluency, whether or not they are currently receiving psychiatric services for their phobia, and either the FAS or FSQ (duration of 15 minutes). This screener is given prior to official consent in order to save ineligible participants time and prevent unnecessary baseline data from being collected. If participants do not meet inclusion criteria, an automatic email will be sent to them notifying them of their exclusion and the reasoning of such. If participants are

eligible, a trigger email will be sent to the researchers to let us know they meet criteria to participate. This screening information will not be used for any other purposes other than to determine inclusion and exclusion; all screening survey responses will be deleted after participant's eligibility has been determined.

If eligible, according to the basic screener, and still interested, the research assistant will send the patient information letter and informed consent form to their home address with a return envelope. If necessary, the researcher will remind them by email to complete the informed consent (2 reminders in total, second being a phone call). The informed consent form will be sent to each participant. The participant will be instructed to sign the consent form and mail it back to us. Once received, we will sign the consent form as well and then make a copy of the consent form. This copy will be mailed back to the participant to keep for their own records.

Upon receiving informed consent, the researcher will send a second survey link to participants via email to complete a baseline measurement. In this baseline measurement, demographic variables (gender, level of education, marital level), FAM (aviophobia) or SPQ (arachnophobia), PHQ, BAI, WSQ, and IRI will be measured (duration of 20 minutes).

If necessary, the researcher will remind them by email to complete the baseline measurement (2 reminders in total, second being a phone call). After the baseline has been completed, participants will be randomized by an independent researcher. The research assistant will notify the participant of which condition they have been randomized to, either the intervention condition or the waitlist condition.

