### **8.6 Follow-up of subjects withdrawn from treatment**

If a subject is withdrawn from treatment, either due to their own decision or the decision of the research staff, they will still be followed-up with. All participants will be included in the intention-to-treat (ITT)-analyses.

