## **9.4 Follow-up of adverse events**

All AEs will be followed until they have abated, or until a stable situation has been reached. Depending on the event, follow up may require additional tests or medical procedures as indicated, and/or referral to the general physician or a medical specialist. SAEs need to be reported till end of study within the Netherlands, as defined in the protocol.

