## **10. STATISTICAL ANALYSIS**

### **10.1 Primary study parameter(s)**

The primary outcome measure (FAS for aviophobia, FSQ for arachnophobia) will be treated as a continuous outcome. Continuous variables will be presented as mean, standard deviation, and minimum and maximum number of observations. Descriptive statistics of demographics and clinical outcomes will be compared between the experimental and control condition. The quantitative analysis of the primary endpoints will be performed on an intention-to-treat basis following the per protocol analysis (PPA) according to CONSORT recommendations and SPIRIT guidelines for reporting results (Chan 2013a, 2013b; Eysenbach et al., 2011). Comparisons will be made between and within the groups for pre- and post-measurement and follow-up. Multiple imputation will be used in dealing with missing data, assuming this is "at random" (Brunton-Smith et al., 2014). We will calculate Clinical Meaningful Change on the FAS (Evans, 1998) and a reliable change criterion (Evans, 1998). We will also calculate the number needed to treat (NNT) based on (Christensen et al., 1986; Cohen, 1972). Standardized effect sizes (Cohen's d) and the confidence intervals are calculated. STATA version 16 will be used for the analyses. The best static analysis procedure to perform the analyses for this RCT will be reviewed before the data is analysed.

Intention-to-treat analysis will be used on continuous scales using repeated measures analysis of variance (ANOVA). Per protocol analysis will be performed by independent sample t-tests. Standardized effect sizes (Cohen's d) and confidence intervals will be calculated. SPSS version 21 will be used for the analyzes. A  $p$ -value  $<0.05$  will be considered to indicate statistical significance.

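### Section 8.4 destroys the data of withdrawers who refuse permission, while 8.6 puts all participants in the ITT analyses; for a randomised refuser both cannot hold.

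*Protocol*

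**What the plan says.** Section 8.4 covers a participant who ends participation early: "s/he will be asked to give permission that the data that were collected until that time point may be included in the ITT-analyses". The consequence of refusal follows: "If the participant refuses to give permission, his/her data will be destroyed".

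Section 8.6 covers people who come off the intervention: "If a subject is withdrawn from treatment, either due to their own decision or the decision of the research staff, they will still be followed-up". It closes without any exception: "All participants will be included in the intention-to-treat (ITT)-analyses".

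Section 10.1 builds the primary analysis on this set: "The quantitative analysis of the primary endpoints will be performed on an intention-to-treat basis". For gaps it says: "Multiple imputation will be used in dealing with missing data", assuming missing at random. It does not mention destroyed records.

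On timing, section 8.3 states: "After the baseline has been completed, participants will be randomized by an independent researcher". The participant is then told the condition, and section 8.2 says double blinding is not possible. Also in 8.3, only those randomised to the intervention receive the 3- and 12-month questionnaires.

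On safety, section 9.4 states: "All AEs will be followed until they have abated, or until a stable situation has been reached". Section 8.4 does not say whether adverse-event records fall within the data to be destroyed.

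**The concern.** An ITT set should be fixed by randomisation. Section 8.4 makes membership conditional on a permission requested at withdrawal, from someone who knows the allocation and has just decided to leave. If refusal is related to how the person fared, the retained set is no longer the randomised comparison, although it would still be reported as ITT.

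This is not a detail that a statistical analysis plan can settle later. The protocol itself fixes the destruction rule, and no later plan can recover a destroyed record. Imputation cannot rebuild it either, since the baseline values go too. Section 8.4 also does not say that arm and withdrawal status survive, although drop-out is one of the trial's stated questions (section 2).

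**Working it through.** **1. The two rules side by side.**

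| Case | 8.4 | 8.6 and 10.1 | Compatible? |
|---|---|---|---|
| Stops the app, stays in the study | does not apply | followed up, in ITT | yes |
| Ends participation, gives permission | data to that point in ITT | in ITT | yes |
| Ends participation before randomisation, refuses | destroyed | not a randomised participant | no harm |
| Ends participation after randomisation, refuses | destroyed | in ITT | **no** |

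The conflict is confined to the last row.

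**2. What is lost, by time of leaving.** FAS and FSQ are measured at baseline, post-test and, in the app arm only, at 3 and 12 months (sections 8.1.1 and 8.3, Table 1).

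- *Before post-test:* no post-test score exists, so only baseline data are destroyed. Had the record been kept, the missing post-test score would have been imputed under missing at random. If leavers and stayers in an arm have similar baseline scores, the imputed values average to the stayers' mean. The estimate is then, in expectation, the same as with the leavers deleted. A simulation of 2 or 5 zero-benefit app-arm leavers (assumed baseline-outcome correlation 0.5, imputation within arm) agreed to two decimals between deletion and imputation in both trials.
- *After post-test:* an observed primary outcome is destroyed. App-arm participants remain in follow-up to 12 months, so their scores stay exposed for about a year. Wait-list participants receive the app after post-test and could also leave then, but they have no further scheduled assessment.

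**3. Size for the second group.** Inputs: d = 0.70 with 48 per arm and d = 0.80 with 36 per arm (section 4.3). The number of refusers k is not in the documents; k = 2 to 5 is an assumption. Suppose the k erased app-arm participants had no benefit and the SD is unchanged. The effect in the full arm is then d, and in the retained set it is d × n/(n − k):

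- Aviophobia: 0.70 × 48/46 = 0.73; 0.70 × 48/43 = 0.78 (rise of 4% to 12%).
- Arachnophobia: 0.80 × 36/34 = 0.85; 0.80 × 36/31 = 0.93 (rise of 6% to 16%).

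**4. Size under no true effect.** Suppose a share r of one arm is erased and those people are 1 SD worse than the retained. The difference shifts by r SD, with SE = √(1/[n(1 − r)] + 1/n).

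- n = 48, r = 0.10: SE = √(1/43.2 + 1/48) = 0.210, shift/SE = 0.48, two-sided error about 7.6%.
- n = 36, r = 0.10: SE = √(1/32.4 + 1/36) = 0.242, shift/SE = 0.41, two-sided error about 7.0%.
- r = 0.05: about 5.7% (n = 48) and 5.5% (n = 36).

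**5. Upper bound on who could be asked.** The planned 40% drop-out gives 0.40 × 48 = 19.2 and 0.40 × 36 = 14.4, so about 19 and 14 per arm. These are ceilings. Someone who simply stops answering reminders need never reach the question in 8.4, and someone who stops the app but stays in the study falls under 8.6.

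**The case against.** The strongest defence is that the sections have different scopes: 8.6 concerns people who stop treatment and are still followed, and 8.4 concerns people who leave the study. This stands as far as follow-up is concerned and narrows the conflict to randomised refusers. It does not remove it, because the last sentence of 8.6 says all participants and 8.4 itself ties ITT inclusion to permission.

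Destruction on request may also be a deliberate ethics or privacy choice. That is possible; the consent pages are not available here, so neither what participants agreed to at entry nor the reason for the rule can be checked. It affects which repair is chosen, not whether the sections need reconciling.

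Three stronger readings are tempting, and the documents do not support them:

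- *That the planned 40% drop-out translates into inflation of 4% to 16%.* Most drop-out need not lead to a refusal. For people without a post-test score, any such inflation comes from informative drop-out analysed under missing at random and would arise with every record kept.
- *That Negative Effects Questionnaire data are lost from early leavers.* That questionnaire is given only at post-test, so someone leaving earlier has none to lose.
- *That 8.4 orders adverse-event records to be destroyed.* It is silent. The sentence follows directly on data for the ITT analyses, adverse events are recorded under 9.2.1, and serious ones go to the ethics committee within set times under 9.2.2. The silence should be closed, but it is not evidence of erasure.

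**Conclusion.** The contradiction is real and visible in the text: for a participant who leaves after randomisation and refuses permission, 8.4 and 8.6 cannot both be followed, and the primary analysis rests on the set they define differently. The exposure that matters is loss of observed post-test scores, and it lasts longer in the app arm.

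Bias is neither certain nor shown to be large. The refusal share is not given and may be zero. The shifts to 0.73-0.78 and 0.85-0.93 hold only for 2 to 5 zero-benefit app-arm participants whose post-test scores are erased. Under no true effect, type I error stays below 6% if 5% of one arm or less is erased, and reaches about 7% to 8% at 10%, assuming those erased are 1 SD worse. The case for acting is that destruction cannot be undone and the repair is cheap.

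**What to change.** **Preferred.** State in 8.4 and in the consent form that withdrawal stops further data collection and that data collected up to then are retained for the ITT analysis. Sections 8.6 and 10.1 can then stand.

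**If erasure on request must stay:**

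- Change 8.6 and 10.1 to 'all randomised participants except those whose data were erased'.
- Keep a non-identifying record of arm, withdrawal date and any adverse event.
- Report the number of erasures per arm.
- Add one sensitivity analysis giving erased participants in either arm zero change from an assumed baseline, such as the arm mean. Their own baseline values would be gone, so an analysis built on those could not be run.

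**In both cases,** state in 8.4 that adverse-event records are not destroyed.

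The cost is protocol and consent-form wording, submitted as an amendment if the protocol is already approved, plus a short log and one sensitivity analysis if erasure stays. The drawback of the preferred option is that participants give permission in advance rather than at withdrawal. The change has to come before withdrawals occur.

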##### 8.4.1 Specific criteria for withdrawal (if applicable)

Not applicable

### **8.5 Replacement of individual subjects after withdrawal**

Not applicable

### **8.6 Follow-up of subjects withdrawn from treatment**

If a subject is withdrawn from treatment, either due to their own decision or the decision of the research staff, they will still be followed-up with. All participants will be included in the intention-to-treat (ITT)-analyses.

### **8.7 Premature termination of the study**

The study will only be prematurely terminated in case of a serious adverse event (SAE, see 9.1) that is the direct result of the study. In this case the accredited METC and the subsidising party will be informed without undue delay. Participants in either condition will be informed by email, with the content of said email being individual to the specific reason of termination. Participants who are still in the active treatment conditions will receive a notification through email explaining that the study has stopped due to unforeseen circumstances and access to all modules will be blocked. All participants will receive information on where they can seek help for their mental health problems. In addition, the study can be terminated prematurely due to ethical concerns or insufficient participant recruitment.

## **9. SAFETY REPORTING**

### **9.1 Temporary halt for reasons of subject safety**

In accordance to section 10, subsection 4, of the WMO, the sponsor will suspend the study if there is sufficient ground that continuation of the study will jeopardise subject health or safety. The sponsor will notify the accredited METC without undue delay of a temporary halt including the reason for such an action. The study will be suspended pending a further positive decision by the accredited METC. The investigator will take care that all subjects are kept informed.

## **9.2 AEs, SAEs and SUSARs**

### **9.2.1 Adverse events (AEs)**

Adverse events are defined as any undesirable experience occurring to a subject during the study, whether or not considered related to ZeroPhobia. All adverse events reported spontaneously by the subject or observed by the investigator or his staff will be recorded.

### **9.2.3 Suspected unexpected serious adverse reactions (SUSARs)**

Not applicable

## **9.3 Annual safety report**

Not applicable

## **9.4 Follow-up of adverse events**

All AEs will be followed until they have abated, or until a stable situation has been reached. Depending on the event, follow up may require additional tests or medical procedures as indicated, and/or referral to the general physician or a medical specialist. SAEs need to be reported till end of study within the Netherlands, as defined in the protocol.

### **9.5 [Data Safety Monitoring Board (DSMB) / Safety Committee]**

Based on the low risk of participation in the study (see also section 13: Structured Risk Analysis), a data safety monitoring board (DSMB) is not required and will not be set up.

## **10. STATISTICAL ANALYSIS**

### **10.1 Primary study parameter(s)**

The primary outcome measure (FAS for aviophobia, FSQ for arachnophobia) will be treated as a continuous outcome. Continuous variables will be presented as mean, standard deviation, and minimum and maximum number of observations. Descriptive statistics of demographics and clinical outcomes will be compared between the experimental and control condition. The quantitative analysis of the primary endpoints will be performed on an intention-to-treat basis following the per protocol analysis (PPA) according to CONSORT recommendations and SPIRIT guidelines for reporting results (Chan 2013a, 2013b; Eysenbach et al., 2011). Comparisons will be made between and within the groups for pre- and post-measurement and follow-up. Multiple imputation will be used in dealing with missing data, assuming this is "at random" (Brunton-Smith et al., 2014). We will calculate Clinical Meaningful Change on the FAS (Evans, 1998) and a reliable change criterion (Evans, 1998). We will also calculate the number needed to treat (NNT) based on (Christensen et al., 1986; Cohen, 1972). Standardized effect sizes (Cohen's d) and the confidence intervals are calculated. STATA version 16 will be used for the analyses. The best static analysis procedure to perform the analyses for this RCT will be reviewed before the data is analysed.

Intention-to-treat analysis will be used on continuous scales using repeated measures analysis of variance (ANOVA). Per protocol analysis will be performed by independent sample t-tests. Standardized effect sizes (Cohen's d) and confidence intervals will be calculated. SPSS version 21 will be used for the analyzes. A  $p$ -value  $<0.05$  will be considered to indicate statistical significance.

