#### **4.3 Sample size calculation**

Aviophobia: An effect size of Cohen's  $d = 0.80$  was found from a meta-analysis of VR treatments for fear of flying (Fodor, 2018). Because ZeroPhobia: Aviophobia is a complete self-help treatment with rudimentary VR glasses, we have taken a slightly more conservative effect size of 0.70 as the starting point for the power calculation. To demonstrate a difference between the experimental and control condition with a standardized effect size of  $d = 0.70$  (tested on both sides), an alpha of 0.05 and a statistical power (1-beta) of 0.80, we have 34 respondents in each condition required (68 respondents in total). Taking into account a drop-out rate of 40% (Donker et al., 2019), we need a total of 96 respondents ( $n = 48$  per condition).

Arachnophobia: An effect size of Cohen's  $d = 1.11 / 1.12$  was found from a meta-analysis of VR treatments for different phobias, including fear of spiders (Opris et al., 2012,

Powers et al., 2008). Because ZeroPhobia: Arachnophobia is a complete self-help treatment with rudimentary VR glasses, we have taken a slightly more conservative effect size of 0.80 as the starting point for the power calculation. To demonstrate a difference between the experimental and control condition with a standardized effect size of  $d = 0.80$  (tested on both sides), an alpha of 0.05 and a statistical power (1-beta) of 0.80, we have 26 respondents in each condition required (52 respondents in total). Taking into account a dropout rate of 40% (Donker et al., 2019), we need a total of 72 respondents ( $n = 36$  per condition).

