### **8.1.3 Other study parameters (if applicable)**

- Demographic variables (gender, age, education level, marital status, employment status).
- System Usability Scale (SUS; Bangor et al., 2008): 10 items about user friendliness of the app. The SUS is composed of 10 statements that are scored on a 5-point scale of strength of agreement. Final scores for the SUS can range from 0 to 100, where higher scores indicate better usability. This means that products that are at least passable have SUS scores above 70, with better products scoring in the high 70s to upper 80s. Truly superior products score better than 90. Products with scores less than 70 should be considered candidates for increased scrutiny and continued improvement and should be judged to be marginal at best. Reliability is good (Bangor et al. 2008). This questionnaire will be completed at post-test.
- User-friendliness of ZeroPhobia as a treatment will be in part measured with the 6-item self-report treatment expectation and satisfaction scale called the

Credibility/Expectancy Questionnaire (CEQ; Devilly & Borkovec, 2000). The CEQ measures expectations of the participants before the start of the treatment. This questionnaire will be used alongside the post-test SUS and NEQ to determine if ZeroPhobia did in fact meet expectations.

- User-friendliness will also be measured using single item questions directly asking about the user experience of ZeroPhobia and the realism of the VR environments. This also includes one open question asking for any other feedback on the app a participant would like to give.
- Igroup Presence Questionnaire (IPQ; Schubert, Friedmann and Regenbrecht 2001), a 14-item questionnaire, which assess realism and “presence” in the VR environment. Each of the items has five response categories from fully disagree (1) to fully agree (5). Chronbach`s alpha is good ( $\alpha = .73$ ). This questionnaire along with some open questions about user experience of the VR environment will be completed at post-test.
- Ecological Momentary Assessment: One question about current anxiety level during exposure in VR
- Usage data from the ZeroPhobia app: frequency and duration of practice during exposure in VR, frequency and duration of time spent in the modules.
- Flight usage questions, including when was the last time you flew on an airplane, how many times have you flown in the past 3/12 months and how long was each of these flights?

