If in the intervention condition, the research assistant will send the VR glasses to the participant by postal delivery, along with usage instructions. The research assistant will email the participant with instructions on how to download the ZeroPhobia app to his/her smartphone. The app is locked with an individual code which will be given to the participant at the start of the intervention. Participants can then begin the ZeroPhobia intervention which they can follow for 6 weeks (5-20 minutes per week, in addition to VRET from module/week 3 onward, which we recommend 10 minutes a day of practice with). When practicing in VRET, participants are asked to fill in one question about their anxiety level before, during, and after VRET (duration: 5 seconds). Participants can follow the intervention at their own pace. Participants will receive weekly automatic reminder emails to begin or continue the intervention from the research assistant. If needed (e.g., with a question about how to use ZeroPhobia or in the unlikely case of distress), participants will be invited to contact the research assistant.

If in the wait-list condition, the participant will be informed that after a six week pause and the completion of a post-test assessment, they can begin the ZeroPhobia program. The wait-list group will undergo the same program procedure as those in the treatment condition. Participants of both conditions will begin the program on the first working Monday after

completing the baseline and being randomized to a condition, meaning participants of both groups will have different start and end times. Both groups will have the same duration of each section, however (see flowchart).

The aforementioned post-test (occurring after 6 weeks of either intervention or pause, or after the completion of module six in the intervention group (for those participants who choose to work through the ZeroPhobia program faster) consists of the FAS and FAM (aviophobia) or FSQ and SPQ, (arachnophobia), PHQ, BAI, IPQ, SUS, CEQ and NEQ, questions regarding whether they received professional treatment during this time, and questions about flight usage (duration: 25 minutes). Two reminders will be given across two weeks to fill in post-test, the first being an e-mail and the second a phone call.

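### Section 10.1 commits to imputation at random with 40% drop-out planned, although only the waitlist arm has to return the post-test to get the app

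*Protocol*

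**What the plan says.** Protocol section 10.1 states for the primary outcome (FAS or FSQ at post-test): "Multiple imputation will be used in dealing with missing data". It adds that the data are assumed missing at random. Sections 10.2 and 10.3 repeat this. None of the three gives an imputation model or names another approach to missing data. The other analysis in 10.1 is a per-protocol t-test.

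Section 4.3 expects heavy loss in both trials: "Taking into account a drop-out rate of 40% (Donker et al., 2019), we need a total of 96 respondents" for aviophobia and "Taking into account a dropout rate of 40% (Donker et al., 2019), we need a total of 72 respondents" for arachnophobia.

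Section 8.3 tells waitlist participants that "after a six week pause and the completion of a post-test assessment, they can begin the ZeroPhobia program", and section 3 says the same. Intervention participants receive their access code at the start. Both arms get the same two post-test reminders, an e-mail and then a phone call.

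Section 8.6 says that people withdrawn from treatment are still followed up and that all participants enter the intention-to-treat analyses. Section 8.4 says that data are destroyed if someone who leaves refuses permission to use them.

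Section 8.1.3 lists app usage data: "frequency and duration of practice during exposure in VR, frequency and duration of time spent in the modules".

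**The concern.** The access rule gives waitlist participants a concrete reason to return the post-test. An intervention participant who has lost interest in the app has no matching reason. For those who work faster than six weeks, the intervention-arm post-test is triggered by finishing module six, which links it further to completing treatment. It is therefore plausible that the arms lose post-tests for different reasons, and that in the app arm the reason is related to how well treatment went.

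Imputation at random fills each gap from people with the same observed characteristics. If arm is one of those characteristics and nothing about use of the app is, a non-responder who hardly used the app is imputed as if they had responded like the app-arm responders. With up to two fifths of post-tests missing, this could move the primary estimate materially. The per-protocol t-test is no check on this: it does not test the missing-data assumption and may err in the same direction.

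**Working it through.** **1. The plan's own figures.** Section 4.3 gives d = 0.70 and 0.80, two-sided alpha 0.05 and power 0.80. A two-sample t-test needs 33.02 per arm, rounded up to 34, and 25.52, rounded up to 26. These match the text: "we have 34 respondents in each condition required (68 respondents in total" and "we have 26 respondents in each condition required (52 respondents in total". The totals of 96 and 72 correspond to multiplying by 1.4 (68 × 1.4 = 95.2; 52 × 1.4 = 72.8). They therefore absorb a loss of 1 − 68/96 = 29.2% and 1 − 52/72 = 27.8%, not 40%. That is a separate matter. Here it matters only that 40% is the loss the protocol itself expects.

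**2. Size of a possible bias.** Let m be the share of app-arm post-tests missing. Let f be the share of the responders' benefit that non-responders truly have. Assume that the planned d holds in responders, that arm is in the imputation model, and that waitlist non-responders resemble waitlist responders given baseline.

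- Imputation at random reports about d.
- The all-randomised effect is d × [(1 − m) + m × f].

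| m | f | factor | aviophobia (reported 0.70) | arachnophobia (reported 0.80) |
|---|---|---|---|---|
| 20% | 0 | 0.8 | 0.56 | 0.64 |
| 20% | 0.5 | 0.8 + 0.1 = 0.9 | 0.63 | 0.72 |
| 40% | 0 | 0.6 | 0.42 | 0.48 |
| 40% | 0.5 | 0.6 + 0.2 = 0.8 | 0.56 | 0.64 |
| 60% | 0 | 0.4 | 0.28 | 0.32 |
| 60% | 0.5 | 0.4 + 0.3 = 0.7 | 0.49 | 0.56 |
| any | 1 | 1 | 0.70 | 0.80 |

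At m = 40% the overstatement is 1/0.6 = 1.67 times (f = 0) or 1/0.8 = 1.25 times (f = 0.5). The ratio depends on m and f only, not on the value of d.

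**3. False-positive risk.** A simulation with no true effect used 3,000 runs and an assumed baseline to post-test correlation of 0.5. The analysis was a baseline-adjusted comparison of observed data, which in expectation is equivalent to imputation at random from arm and baseline.

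| missing, app / waitlist | correlation of missingness with worse outcome | type I error, N = 96 | type I error, N = 72 |
|---|---|---|---|
| 40% / 20% | none | 5% | 5% |
| 40% / 40% | 0.3 in both arms | 5% | 5% |
| 40% / 20% | 0.3 in app arm only | 12% | 10% |
| 40% / 20% | 0.5 in app arm only | 26% | 21% |
| 40% / 40% | 0.5 in app arm only | 23% | 19% |

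Unequal rates alone do no harm, and neither does outcome-related loss that is the same in both arms. In these runs the harm appears when missingness is related to outcome in one arm and not in the other.

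**The case against.** **Details belong in a statistical analysis plan.** Imputation models and sensitivity analyses are often placed there, and none is at hand. Section 10.1 also says the analysis procedure will be reviewed before analysis. This stands as far as it goes: the absence of a sensitivity analysis is not the finding. The finding is that the protocol commits to one assumption that its own access rule makes doubtful. The review sentence does not mention missing data.

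**Stopping the app is not the same as missing the post-test.** This is right and it narrows the point. The post-test is due at six weeks whether or not module six is finished, there are two reminders, and section 8.6 keeps people who stop treatment in follow-up. Those who answer contribute real outcomes, and the imputation draws on them too. A reader might infer that the intention-to-treat result estimates the effect as if everyone had continued treatment. The documents do not support that.

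**No figure shows that loss will fall on the app arm.** Also right. Section 4.3 gives one rate and equal arms. A reader might infer that missing outcomes will concentrate in the app arm and that the estimate is biased. The first is a reasonable expectation from the incentives, and the second depends on it and on non-responders having benefited less.

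**The imputation model is not stated.** So it cannot be said that the protocol imputes within arm from baseline variables only. Adding usage data would be fully compatible with section 10.1 as written.

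**The effect sizes are not described as completer effects.** True. Section 4.3 presents them as values lowered from meta-analyses, so applying them to responders is an assumption made here.

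**Conclusion.** The point holds in conditional form. The protocol fixes missingness at random as its only stated assumption, plans for 40% drop-out, and gives only one arm an incentive to supply the primary outcome. That makes the assumption doubtful enough to be worth strengthening and testing.

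The direction of the risk is towards the app, provided that arm is in the imputation model and that app-arm non-responders benefited less than responders. At 40% app-arm missingness the illustrative overstatement runs from none (equal benefit) through 1.25 times (half the benefit) to 1.67 times (no benefit). The last is the extreme case and should not be read as the expected one. App-arm participants who stop the app but return the post-test are unaffected. The missingness by arm and the benefit in non-responders are both unknown from the documents.

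**What to change.** In section 10.1, before any outcome is seen:

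- Keep multiple imputation as the primary method. State that it is done separately by arm. In the intervention arm, include the app usage data already collected as auxiliary variables. Add in-app fear ratings where they exist; they start only with VR exposure in module 3, so people who stop earlier have none.
- Pre-specify one reference-based sensitivity analysis, in which missing app-arm post-tests are drawn from the waitlist distribution given baseline. Report it beside the primary result, with missingness by arm.
- State that it serves to judge robustness and is not a second significance criterion. If non-responders truly gained nothing at 40% missingness, effects of 0.42 and 0.48 would have only about 53% and 52% power even with complete data on all 96 or 72.

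The cost is a paragraph of text and a few hours of programming, with no new data collection. There are two downsides. The reference-based estimate is conservative. The auxiliary variables must also be few, because at 40% loss only 48 × 0.6 = 28.8 or 36 × 0.6 = 21.6 app-arm post-tests are observed.
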